### Treatment process measures

#### Self-efficacy: Pain Self Efficacy Questionnaire (PSEQ)

Self-efficacy refers to a person’s confidence in their ability to perform activities despite pain [46] and has been identified as an important mediator in the relationship between pain and disability [47]. The PSEQ features ten items that produce a total score between 0 to 60, with higher scores indicating greater self- efficacy. Analyses have shown the PSEQ to have strong psychometric properties [48].

#### Pain catastrophising: Pain Catastrophising Scale (PCS)

Catastrophisation is defined as an elevated negative cognitive response to painful stimuli [49]. Change in pain catastrophising has been shown to mediate reductions in pain and disability [50]. The PCS consists of 13 items that refer to thoughts and feelings related to pain. Respondents are asked to rate the degree to which they experience each item on a 5-point scale 0 (not and all) to 4 (all the time) and items are summed to give a potential total score of 52. There are also three subscales within the PCS; rumination, magnification and helplessness. The PCS has been shown to have adequate to excellent internal consistency and validity [49, 51].

#### Fear avoidance: Tampa Scale of Kinesiophobia (TSK)

Fear avoidance beliefs have been shown to be associated with higher levels of disability [52] and worse prognosis in patients with low back pain [53]. The TSK is a 17-item questionnaire, which assesses fear of movement and re-injury. It has been reported to be a reliable and valid measure of fear of movement in individuals with chronic pain [54].

#### Chronic Pain Acceptance Questionnaire – 8 (CPAQ-8) and Committed Action Questionnaire – 8 (CAQ-8)

Pain acceptance and committed action are components of the ACT model and may be potential mediators of change, related to ACT. The CPAQ-8 is a shortened version of the original 20-item CPAQ, with two subscales; activity engagement and pain willingness. Each item is scored from 0 (never true) to 6 (always true). The CPAQ has been shown to be valid and reliable, with good internal consistency and sensitivity to change [55] and the shortened version has demonstrated a sound factor structure and similar psychometric properties to the CPAQ [56, 57]. The CAQ-8 is a shortened version of the original 18-item Committed Action Questionnaire, which assesses an individual’s persistence and flexibility in acting in the direction of valued goals [58]. The items are rated from 0 (never true) to 6 (always true). The CAQ-8 has shown comparable reliability and validity to the original version [59].

### Physical activity outcomes

Physical activity will be measured using a Fitbit Zip^TM^ wearable activity tracker. The trackers provide an objective indicator of physical activity behaviour and avoid common sources of error in subjective measurement (e.g. self-report measurement). The Fitbit Zip^TM^ has an internal memory that can store data for up to 30 days and data can be transferred wirelessly to the Fitbit website via a smartphone application or by computer using the dongle provided. The ease of download of information from the Fitbit website will enable the data to be captured remotely.

Data collected will include average weekly step count, distance travelled and active minutes. Participants will be provided with the activity tracker at the baseline appointment and instructed in how to use it. The activity trackers will be worn by participants for 1 week prior to starting the interventions and for the full duration of the interventions (8 weeks in total). The main time points for analysis will be the baseline week and the last week of the intervention.

The Fitbit Zip^TM^ has been found to be a valid measure of free-living physical activity in healthy adults [60]. A recent study comparing the reliability and validity of ten consumer activity trackers reported excellent test-retest reliability of the Fitbit Zip^TM^, which was also reported to be the most valid of the ten trackers [61]. To our knowledge this will be the first RCT to collect physical activity data related to the effect of a combined ACT and exercise intervention on physical activity patterns measured objectively in a chronic pain cohort.

### Statistical analysis

Outcome analyses will be conducted by a professional academic statistician (RS) who will be blinded to treatment group allocation. A statistical analysis plan (SAP) will be drafted outlining the precise model to be applied and finalised before the last patient assessment is completed. No interim analyses will be conducted. Descriptive statistics will be calculated for all outcome measures at each time point, including for continuous variables: means, standard deviations, or medians with ranges of scores; and for categorical variables: frequencies and percentages.

#### Analyses of effectiveness of primary and secondary outcomes

Descriptive and inferential statistics will be obtained using the appropriate statistical methods that seek to address our identified objectives. The primary analysis will compare the effect of the interventions on the primary outcome; pain interference at 12 weeks post completion of the intervention. All outcome analyses will be conducted according to an intention-to-treat principle, i.e. all randomised participants will be included in the main analysis and will be analysed as randomised, regardless of protocol adherence. Secondary analysis will include the analysis of the primary outcome post intervention and analysis of the secondary and treatment process outcomes detailed previously post intervention and at 12-week follow-up. Linear mixed models on the outcome measures over time will be fitted to evaluate the effectiveness of both interventions, which intrinsically adjusts for pre-treatment scores. Statistical significance will be assessed from a *p* value < 0.05 from the group by time interaction term. For all tests, two-sided *p* values will be used, which will be reported to four decimal places with *p* values < 0.001 reported as *p* < 0.001. The Bonferroni method will be used to appropriately adjust the overall level of significance for multiple secondary outcomes as applicable. In the case of a significant result, planned contrasts of the group effects at post treatment and at 12-week follow-up will be used to investigate the direction and pattern of effects, and outlined in advance in the SAP. As a key component of the reporting of the analyses of outcomes, the mean changes (irrespective of statistical significance) and correlations of the measures between the assessment time periods will be obtained. An up-to-date version of SPSS will be used to conduct the analyses.

#### Missing data

Careful attention will be paid to ensure that all participants are fully assessed at all time points. Baseline data will be checked for missing data by the lead researcher at the baseline assessment and participants will be encouraged to complete any missing answers. It is hoped that this process will help minimise missing data at follow-up as the senior researcher will be able to clarify any ambiguous questions face-to-face at baseline. However, the trial supervisor will follow up on any missing data by telephone or post at the subsequent time points. For the purpose of secondary analysis and as a sensitivity analysis for the primary outcome, multiple imputation will be considered for any measure with over 5% missing data, using a chained equations method robust to non-normally distributed data. This will be fully reported in line with the updated CONSORT recommendations [32]. All primary and secondary outcomes (excluding physical activity data), treatment process measures and pre-selected baseline covariates (age, gender, work and educational status, pain-intensity, anxiety, depression, self-efficacy and catastrophising) will be included in the imputation model. These baseline covariates have been selected based on studies that have examined predictors of outcome of multidisciplinary treatment in chronic pain [62, 63] .

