#### Sensitivity analysis

The following sensitivity analyses will be undertaken and reported:*A per-protocol analysis*: the per-protocol analysis will exclude participants found to be ineligible after randomisation and those who attend less than 50 % of the intervention. Both intention-to-treat and per-protocol analysis sets will be reported and superiority will be determined only if demonstrated with the primary intention to treat analysis*Multiple imputation of missing data*: the results from a complete case analysis will be compared to those from imputed data to assess whether they change the interpretation of findings

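### The variables listed for the imputation model leave out randomised arm, so the imputed sensitivity and secondary analyses would be pulled toward no effect

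*Protocol article*

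**What the plan says.** In the protocol article, the Missing data section gives multiple imputation two uses: secondary analysis, and "as a sensitivity analysis for the primary outcome, multiple imputation will be considered for any measure with over 5% missing data". It then states the model's contents: "All primary and secondary outcomes (excluding physical activity data), treatment process measures and pre-selected baseline covariates". The covariates are named: "age, gender, work and educational status, pain-intensity, anxiety, depression, self-efficacy and catastrophising) will be included in the imputation model". Physical activity data are expressly excluded. Randomised arm is not mentioned, and no section says that imputation is done separately by arm.

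The Sensitivity analysis section states how the result will be used: "the results from a complete case analysis will be compared to those from imputed data to assess whether they change the interpretation of findings". The same section lets superiority rest on the primary intention-to-treat analysis alone.

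The section on analyses of effectiveness specifies linear mixed models over time, judged on the group by time interaction, and says that "all randomised participants will be included in the main analysis and will be analysed as randomised, regardless of protocol adherence".

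**The concern.** An imputation model should contain every term that the analysis model estimates. Here the analysis estimates a difference between arms, and the listed imputation variables do not include arm. Baseline covariates cannot stand in for it, because randomisation makes them independent of arm. Post-intervention outcomes and process measures can carry part of the arm effect, but only where they were observed and only as far as they predict the 12-week score.

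What is at stake is the reading of the sensitivity analysis. If the imputed estimate is smaller than the complete-case estimate merely because arm was left out, a real effect may be reported as not robust to missing data. Secondary and process outcomes analysed on imputed data would be attenuated in the same way.

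**Working it through.** **Inputs from the protocol (Sample size).** Difference 1 unit, SD of improvement 2 units, 80% power, type I error 0.05, 64 per group, 20% attrition allowance, 80 per group.

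**The plan's own figure.** The Missing data section gives no figure to reproduce. The sample size does reproduce: an exact two-sample *t* test with standardised difference 1/2 = 0.5 needs 63.77, so 64 per group, and 64/0.8 = 80.

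**Assumptions not in the protocol.** Score SD 2 at each time, and baseline to 12-week correlation 0.5. These give an SD of change of 2 × √(2 × (1 − 0.5)) = 2, which matches the protocol. Baseline to post-intervention correlation is 0.5, and post-intervention to 12-week correlation is 0.5 or 0.7. Data are missing completely at random, and the true 12-week difference is 1 point. Only the interference score at three times is modelled, not the full set of measures.

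**Hand calculation.** Let *m* be the fraction missing at 12 weeks, *d* the true post-intervention difference, and *b* the slope of the 12-week score on the post-intervention score given baseline. Imputing without arm gives approximately

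estimate = (1 − *m*) × 1 + *m* × *b* × *d*,

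with the second term zero if the post-intervention score is missing too. The slope is *b* = (r12 − r01 × r02)/(1 − r01²), where 0, 1 and 2 denote baseline, post intervention and 12 weeks.

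- r12 = 0.5: *b* = (0.5 − 0.25)/0.75 = 1/3. With *m* = 0.2 and *d* = 1, the estimate is 0.8 + 0.2/3 = 0.87.
- r12 = 0.7: *b* = (0.7 − 0.25)/0.75 = 0.6. With *m* = 0.2 and *d* = 1, the estimate is 0.8 + 0.12 = 0.92.
- No follow-up data: 0.80.

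**Simulation with r12 = 0.7.** 80 per arm, 1,500 trials per row, 10 imputations by Bayesian normal regression, 12-week score analysed adjusting for baseline. Entries are the mean estimated reduction.

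| Missing at 12 weeks | Post-intervention score | *d* | Hand | Arm omitted | Arm included |
|---|---|---|---|---|---|
| 5% | missing too | 1 | 0.950 | 0.954 | 1.006 |
| 5% | observed | 1 | 0.980 | 0.976 | 0.994 |
| 5% | observed | 0.5 | 0.965 | 0.969 | 1.004 |
| 5% | observed | 0 | 0.950 | 0.953 | 1.004 |
| 20% | missing too | 1 | 0.800 | 0.790 | 0.993 |
| 20% | observed | 1 | 0.920 | 0.918 | 0.993 |
| 20% | observed | 0.5 | 0.860 | 0.857 | 0.993 |
| 20% | observed | 0 | 0.800 | 0.802 | 1.006 |
| 30% | missing too | 1 | 0.700 | 0.704 | 1.013 |
| 30% | observed | 1 | 0.880 | 0.885 | 0.995 |
| 30% | observed | 0.5 | 0.790 | 0.799 | 1.010 |
| 30% | observed | 0 | 0.700 | 0.697 | 1.002 |

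The complete-case estimate stays between 0.99 and 1.01 in every row. With 20% missing and no post-intervention score, power of the imputed analysis is 0.77 with arm omitted and 0.88 with arm included.

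**Simulation with all correlations 0.5.** 800 trials per cell, 5 imputations, 20% missing, *d* = 1. With arm omitted, the estimate is 0.881 if the post-intervention score is observed, 0.829 if half of those missing also lack it, and 0.794 if all do. With arm included it is 1.005 to 1.008.

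**The case against.** The strongest reply is that the list is not stated to be exhaustive. It says what goes in, not that nothing else does. Arm is the factor in the analysis model, so the authors may have taken it for granted, and the Statistical analysis section leaves the precise model to an SAP that is not shown. This stands in part: the defect is an omission from a stated list, not a statement that arm is excluded. But the list goes down to individual covariates and names an exclusion, so anyone following it would have no reason to add arm.

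It can also be said that imputation is only conditional: "multiple imputation will be considered for any measure with over 5% missing data". The Sensitivity analysis section, however, commits to carrying out and reporting the comparison.

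Several stronger readings are tempting, and the protocol does not support them:

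- *The trial's main conclusion is biased.* The primary mixed model does not use the imputed data, and superiority rests on that analysis alone. An attenuated sensitivity estimate cannot create a positive result.
- *Imputed scores are drawn as if the arms did not differ.* This is true only conditional on the listed variables. Observed post-intervention outcomes and process measures carry part of the effect.
- *The bias has a fixed size at the planned missing rate.* The 20% is an attrition allowance for sample size, not a forecast of missing 12-week scores, and the size moves with correlations that the protocol does not give.
- *The complete-case comparator departs from intention to treat.* The phrase in "the results from a complete case analysis will be compared to those from imputed data" is not defined and could mean the mixed model without imputation.
- *Failure to test the missing-at-random assumption is an error.* The protocol misstates nothing here, and such an analysis is commonly left to the SAP.

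**Conclusion.** The point holds in a limited form. Followed as listed, the imputation model attenuates the imputed sensitivity analysis of pain interference and any imputed secondary analyses. With a true 1-point difference, the loss is about 2% to 5% at 5% missing, 8% to 21% at 20% missing, and 11% to 30% at 30% missing. It approaches the missing fraction itself when those missing at 12 weeks have no follow-up data, or when the arms do not differ post intervention.

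These sizes rest on the assumed SD of 2, correlations of 0.5 to 0.7, data missing completely at random, and a single outcome followed over time. Other correlated outcomes in the full model could reduce them. The practical harm is a possible false signal of fragility in the planned comparison, so the correction is worth making but is not critical to the trial's main result.

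**What to change.** In the Missing data specification, state that randomised arm enters the imputation model as a coded A/B label. This is compatible with the blinded statistician: the mixed model needs a group variable in any case, and the label does not reveal which treatment is which. In the simulations, adding arm as a main effect restored the estimate to 0.99 to 1.01.

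Imputing separately by arm is an alternative if numbers allow. With 80 per arm and many measures at up to three times plus nine covariates, the chained equations could be unstable, so the main effect is the safer default.

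The cost is one clause of text and one extra variable in the imputation call, with no new data. The protocol says the SAP will be finalised before the last patient assessment, so the clause can be settled there before any analysis.

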#### Sensitivity analysis

The following sensitivity analyses will be undertaken and reported:*A per-protocol analysis*: the per-protocol analysis will exclude participants found to be ineligible after randomisation and those who attend less than 50 % of the intervention. Both intention-to-treat and per-protocol analysis sets will be reported and superiority will be determined only if demonstrated with the primary intention to treat analysis*Multiple imputation of missing data*: the results from a complete case analysis will be compared to those from imputed data to assess whether they change the interpretation of findings

#### Analysis of physical activity data

The following data will be collected for each trial participant at baseline and on completion of the treatment: average daily step count, distance travelled and active minutes. Only those participants who have worn the device for at least 4 out of 7 days during the baseline and final week will be included in the analyses. The number of participants reaching the global recommendations for physical activity for health [64] will also be recorded. Descriptive statistics will be obtained for the Fitbit variables at baseline and by treatment arm. Linear mixed models will be used to analyse the change in measures between groups.

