### Randomisation

Randomisation will take place after baseline measures have been assessed as recommended by the Consolidated Standards of Reporting Trials (CONSORT) guidelines [32]. Randomisation will be coordinated by the trial supervisor (CD), who will have no involvement in eligibility screening, enrolment or treatment processes. On receipt of signed consent forms and baseline measures, participants will be given a unique code and randomised using an online randomisation database [33]. The computer-generated randomisation schedule will apply a permuted block design to ensure that the groups are balanced periodically. The block size will be concealed until after the primary endpoint has been analysed. The randomisation list will remain with the trial supervisor for the full duration of the study. The list will be stored in an encrypted file on a password-protected computer in the trial supervisor’s office to ensure concealment of allocation. Allocation of participants will be communicated to administrative staff in the pain clinic by the trial supervisor via email. The administrative staff will store this allocation list in an encrypted file, on a password-protected computer in the pain clinic administrative office. Participants will be informed of their group allocation in writing by the administrative staff, who will send notification in sealed, opaque envelopes.

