### Data collection methods

Data will be collected via self-report questionnaires at baseline (t_0_), post intervention (t_1_) and at 12-week follow-up (t_2_). Physical activity patterns will be measured objectively using Fitbit Zip™ (available from: http://www.fitbit.com) activity trackers and recorded from 1 week prior to commencing treatment through to completion of the intervention.

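### The activity-tracker analysis keeps only participants with valid wear in both the baseline and the final week, which conflicts with the intention-to-treat rule set for all outcomes

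*Protocol article*

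**What the plan says.** In the protocol article, the section Analysis of physical activity data sets the inclusion rule: "Only those participants who have worn the device for at least 4 out of 7 days during the baseline and final week will be included". It then plans linear mixed models for the change between groups. The section Physical activity outcomes names two main time points: "The main time points for analysis will be the baseline week and the last week of the intervention".

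The section Analyses of effectiveness of primary and secondary outcomes states the general principle: "All outcome analyses will be conducted according to an intention-to-treat principle, i.e. all randomised participants will be included in the main analysis". It adds that participants "will be analysed as randomised, regardless of protocol adherence". No exception is made for tracker data.

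The section Missing data lists what enters the imputation model: "All primary and secondary outcomes (excluding physical activity data), treatment process measures and pre-selected baseline covariates". The section Sensitivity analysis offers a per-protocol set and a comparison of complete cases with imputed data. Neither addresses the tracker rule. Step count, distance and active minutes form a between-arm comparison under Secondary objectives.

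On timing, Data collection methods says activity is "recorded from 1 week prior to commencing treatment through to completion of the intervention", and Randomisation says "Randomisation will take place after baseline measures have been assessed".

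**The concern.** A minimum number of wear days is a sensible way to decide whether a week's average is usable. The fault is that the rule removes the whole participant when either week fails. Wear in week 8 depends on what happens after randomisation: whether the person is still attending, still motivated and still charting activity. Selecting on it gives up the protection of randomisation for this outcome.

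The trial is unblinded, and weekly contact is 3.5 h in one arm and 1.5 h in the other, so wear or retention could plausibly differ by arm. Elsewhere the protocol handles adherence the other way round. Exclusion for low attendance is only a sensitivity analysis, and superiority is judged on the intention-to-treat set. For activity, the adherence-selected set is the sole analysis.

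At stake is a secondary objective that the Discussion presents as novel and highly relevant. The primary outcome is not affected.

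**Working it through.** **1. The plan's own figures.** The section Sample size uses a difference of 1, SD 2, two-sided alpha 0.05 and power 80%, so d = 0.5. The normal approximation gives n = 2 × (1.960 + 0.842)² × 2² / 1² = 62.8, hence 63 per group. The two-sample t test gives 63.8, hence the stated 64. Allowing for attrition, 64 / 0.80 = 80 per group, 160 in total. These reproduce. They concern the primary outcome; no figure is given for the tracker analysis.

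**2. The sections side by side.**
- The general rule covers all outcome analyses and all randomised participants, whatever their adherence.
- The tracker rule covers only those with valid wear in two named weeks, the second after treatment has been delivered.
- No imputation or sensitivity analysis brings the others back.

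Both rules cannot be followed for step count, distance and active minutes. With every included participant observed at both main time points, a two-time-point mixed model with a group-by-time term is in effect a comparison of mean change scores. The model's usual advantage, using people with one observation, cannot operate.

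**3. Precision (assumed wear rates).** Let p be the share with valid wear in both weeks, equal in both arms. Then 80p per arm are analysed. Power is for a t test at d = 0.5, borrowed from the primary outcome because none is given for activity.
- p = 90%: 144 of 160, power 85%
- p = 80%: 128, power 80%
- p = 70%: 112, power 75%
- p = 60%: 96, power 68%
- p = 50%: 80, power 60%

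**4. What a one-valid-week rule would add.** Assume valid wear of 85% at baseline and 70% in the final week.
- If independent: both weeks 0.85 × 0.70 × 160 = 95; final week only 0.15 × 0.70 × 160 = 17; baseline only 0.85 × 0.30 × 160 = 41. Any valid week: 153.
- If everyone who fails at baseline also fails in the final week: both weeks 0.70 × 160 = 112; any valid week 0.85 × 160 = 136.

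Under independence the 58 regained are not all equally informative. The 17 supply a final-week value directly. The 41 add little unless their intermediate weeks are used.

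**5. Selection bias (assumed).** Suppose there is no true effect, staying in the analysis set follows a normal threshold, and its correlation with activity change is ρ in both arms. The mean change among those kept is shifted by ρ × φ(z)/p, in SD units, where p is the share kept and z the matching normal quantile. The values of φ(z)/p are 0.350 at p = 0.80, 0.497 at 0.70 and 0.644 at 0.60.
- 80% v 70%: ρ × (0.497 − 0.350) = 0.03 at ρ = 0.2 and 0.07 at ρ = 0.5
- 80% v 60%: ρ × (0.644 − 0.350) = 0.06 at ρ = 0.2 and 0.15 at ρ = 0.5
- 80% v 80%: 0

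With positive ρ, the arm that loses more people looks better.

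**6. Timing of the baseline week.** The tracker is handed out at the baseline appointment, before randomisation and up to 4 weeks before treatment, with wear to begin a week or more ahead of the first session (section Baseline). Randomisation is triggered by receipt of consent forms and baseline measures, and allocation is then sent by letter. If the baseline week is the one directly before session 1, some of it may follow the letter. If it is an earlier week, it need not. The text does not say which.

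**The case against.** The best defence is that the valid-wear threshold is prespecified, that the final week matches an objective about activity after treatment, and that the precise model is left to an SAP not shown here. This largely stands. The threshold should be kept and the final week is a proper target. The two time points are called the main ones, so it would be too strong to infer that the intermediate weeks are discarded. But the inclusion rule itself is fixed in the protocol, not deferred.

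It can also be said that the intention-to-treat sentence speaks of the main analysis and so means the primary outcome. Its opening words, "All outcome analyses will be conducted according to an intention-to-treat principle", are wider than that, and it sits in a section covering secondary outcomes too.

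A reader might infer that the activity comparison is biased. The documents do not show this. They hold no wear or retention data, the difference in contact hours is only a reason for suspicion, and the calculation gives zero when retention and its link with activity change are equal across arms. The loss of precision needs no such difference.

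A reader might also infer that the baseline tracker week falls after randomisation. That is not established: the device is issued before randomisation, wear may start earlier than the week before treatment, and the section Randomisation puts baseline measures first. What stands is that the order is not fixed.

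**Conclusion.** The concern holds for the inclusion rule. The tracker section contradicts the intention-to-treat statement, selects on a post-randomisation behaviour, and has no repair elsewhere in the protocol. The consequence is fewer participants analysed (80 to 144 of 160 under assumed both-week wear of 50 to 90%) and a possible spurious difference of roughly 0.03 to 0.15 SD if retention is 80% in one arm and 60 to 70% in the other with ρ of 0.2 to 0.5. All of these rates and correlations are assumptions. The issue deserves correction but is confined to a secondary objective.

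On timing, the supportable conclusion is narrower: part of the baseline week may follow known allocation, and the sections on data collection, baseline, randomisation and physical activity outcomes need to be reconciled.

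**What to change.** In the SAP:
- Keep the four-day rule as the definition of a valid week, and set any week below it to missing.
- Include every randomised participant with at least one valid week in the linear mixed model, using the recorded intermediate weeks where helpful, with the between-arm contrast in the final week as the estimate.
- Report valid wear by week and arm.
- Keep the both-weeks set as a sensitivity analysis.
- State how the tracker baseline week relates to randomisation and to notification of allocation. Where the recorded data allow, use days before notification as baseline.

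The cost is analysis wording and the use of data already being collected. The SAP is to be finalised before the last patient assessment and recruitment was still open at publication, so there was time to do it. The estimate would rest on a missing-at-random assumption, which weakens the selection problem without removing it, and participants with only a baseline week add little.

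Holding back allocation letters to secure a clean baseline week is not needed for this fix. Done during recruitment, it would give early and late participants different baseline definitions and might require a formal amendment.
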